## 5 Ethics and legal aspects

### 5.1 Independent ethics committee and regulatory authority

The clinical study protocol and any substantial amendments will be presented to an Independent Ethics Committee (IEC) and the responsible regulatory authority for review.

Information provided to the subjects and recruitment advertisements (if applicable) will also be reviewed by the IEC.

The positive vote of the IEC and the approval of the regulatory authority will be obtained prior to the start of the study.

A list of IECs consulted will be provided in the clinical study report / Trial Master File.

### 5.2 Ethical and legal conduct of the study

The study will be performed in accordance with the study protocol, the ethical principles that have their origin in the current accepted version of the Declaration of Helsinki and in accordance with ICH GCP and applicable local laws and regulations.

### 5.3 Subject information and consent

Written informed consent must be obtained from subjects prior to participation in the study and prior to completion of any study-related procedure.

The subjects will voluntarily confirm their willingness to participate in the study, after having been informed by a physician in writing and verbally of all aspects of the study that are relevant to the subject's decision to participate. They will be informed about legal requirements concerning data protection and have to agree to the direct access, recording and processing of their personal data which includes special categories of data such as health data. Moreover, they will be informed that withdrawal of their informed consent does not impact data collected up to the point of withdrawal, which will be retained and analyzed. The subject can at any time object in full to the processing of their data outside the protocol for research purposes only.

|  |  |                                                                                                                  |
|--|--|------------------------------------------------------------------------------------------------------------------|
|  |  | CRS Study No.: 090/18-03.MT
Sponsor Study No.: AT1001-035
EudraCT No.: 2018-003684-57 |
|--|--|------------------------------------------------------------------------------------------------------------------|

The informed consent form for study participation including the data protection declaration of consent has to be signed and personally dated by the subject and by the investigator prior to any study -specific procedures. A copy of the signed informed consent form will be given to the subject.

Before informed consent is obtained, the investigator has to provide the subject sufficient time and opportunity to inquire about details of the study and to decide whether or not to participate in the study. All questions about the study have to be answered to the satisfaction of the subject.

The subjects will be informed by a physician in a timely manner if new information becomes available that may be relevant to their willingness to continue participation in the study. The communication of this information will be documented. The subjects will receive a copy of any amendments to the written information and a copy of the signed and dated consent form updates.

Subjects will be informed that they are free to withdraw from the study at any time at their own discretion without having to provide reasons for this decision.

## **7 Introduction**

### **7.1 Background**

#### Fabry disease

Fabry disease is a progressive X-linked lysosomal storage disorder with an estimated prevalence of 1:117,000 up to 1:40,000 which affects males and females. Fabry disease-causing gene encoding  $\alpha$ -galactosidase A (*GLA*) variants result in a

deficiency of the lysosomal enzyme  $\alpha$ -galactosidase A ( $\alpha$ -Gal A) that is required for glycosphingolipid substrate (e.g., globotriaosylceramide [GL-3], lyso-Gb3) metabolism. Reduced  $\alpha$ -Gal A activity is, therefore, associated with the progressive accumulation of substrate in vulnerable organs and tissues, which leads to the morbidity and mortality associated with Fabry disease; however, initiation of therapy in the early stages of the disease with life-long treatment may provide an opportunity to slow disease progression.

The clinical manifestations of Fabry disease span a broad spectrum of severity and seem to be associated with residual  $\alpha$ -galactosidase ( $\alpha$ -Gal A) activity levels that vary widely according to the specific Fabry disease-causing genotype and the specific genetic background of a given patient.

Individuals with classic Fabry disease have little or no detectable  $\alpha$ -Gal A activity levels and are the most severely affected. If these patients are not treated, their life expectancy is reduced and death usually occurs in the third to fifth decade of life from renal failure, cardiac dysfunction, or stroke.

Enzyme replacement therapy and Galafold® are commercially available treatments for Fabry disease. Details on Galafold® are provided in [Section 7.2](#).

## 7.2 Description of the investigational medicinal product

Migalastat hydrochloride (HCl) (Galafold®) is a potent, competitive, and reversible inhibitor of  $\alpha$ -Gal A.

Galafold® is currently licensed in Europe, Switzerland, Israel, Australia, Canada, Japan, South Korea, and the United States for the treatment of adults with a confirmed diagnosis of Fabry disease. Additional Marketing Applications are currently under review.

Preclinical *in vitro* and *in vivo* pharmacology studies have demonstrated that migalastat is a pharmacological chaperone for  $\alpha$ -Gal A that selectively and reversibly binds to the active site of both Wild Type and specific mutant forms of  $\alpha$ -Gal A.

The recommended dosage regimen is 150 mg migalastat HCl (equivalent to 123 mg migalastat free base) once every other day at the same time of day.

### Safety and tolerability

The most common adverse reaction in clinical studies was headache, which was experienced by approximately 10% of patients who received migalastat.

Very common adverse reactions ( $\geq 1/10$ ) were: abdominal pain, diarrhoea, nausea, fatigue, pain, dizziness and headache.

Common adverse reactions ( $\geq 1/100$ ,  $< 1/10$ ) were: rash and pruritus.

 Updated in consistency with update of Investigator's Brochure (Version 17)  
Integrated Clinical Study Protocol, Final 3.0, 29 Aug 2019

In clinical studies, to date, 3 serious adverse events (SAEs) considered possibly related to migalastat have been reported: fatigue and paresthesia in one subject and proteinuria in one subject.

### Pharmacokinetics

The absolute bioavailability (AUC) for a single oral 150 mg migalastat HCl dose was approximately 75%. Following a single oral dose of 150 mg migalastat HCl solution, the time to peak plasma concentration was approximately 3 h. Plasma migalastat exposure (AUC0-∞) and Cmax demonstrated dose-proportional increases at migalastat HCl oral doses from 50 mg to 1250 mg.

In healthy volunteers, the volume of distribution (Vz/F) of migalastat following ascending single oral doses (25-675 mg migalastat HCl) ranged from 77 to 133 L, indicating it is well distributed into tissues and greater than total body water (42 L). There was no detectable plasma protein binding following administration of [C]-migalastat in the concentration range between 1 and 100 μM.

Three minor (hydrolyzed O-glucuronide) metabolites have been elucidated with no one metabolite comprising more than 6% of the dose. Migalastat has neither been shown to induce or inhibit cytochrome P450 (CYP) isoenzymes, nor is it a substrate for P-glycoprotein (P-gp).

A pharmacokinetic (PK) study in healthy volunteers with 150 mg [C]-migalastat HCl revealed that approximately 77% and 20% of the radiolabeled dose were recovered in urine and feces, respectively.

Migalastat is rapidly cleared from plasma (apparent total plasma clearance of drug after extravascular administration [CL/F] approximately 4 to 6 L/h) with a mean half-life of approximately 4 h.

Further details can be found in the latest available version of the Investigator's Brochure (IB) of AT1001 (migalastat HCl), which contains comprehensive information on the study drug and in the Summary of Product Characteristics (SmPC) of Galafold®.

## **7.3 Rationale of the study**

Galafold® currently is not recommended for use in patients with Fabry disease who have estimated glomerular filtration rate (eGFR) less than 30 mL/min/1.73 m^2.

Migalastat is primarily excreted unchanged in urine. Following a single oral dose of 150 mg migalastat HCl in subjects with mild (GFR ≥60 and <90 mL/min/1.73 m^2), moderate (GFR ≥30 and <60 mL/min/1.73 m^2), or severe (GFR ≥15 and <30 mL/min/1.73 m^2) renal impairment, mean plasma migalastat AUC0-∞ increased with degree of renal impairment (up to 4.3-fold). Cmax was unchanged across groups. Plasma migalastat t1/2 increased significantly and plasma clearance decreased significantly with worsening renal function (AT1001-015). Insufficient data are available in subjects with substantial renal impairment to make recommendations

regarding dosing adjustments in these subjects. Migalastat has not been studied in dialysis subjects.

The rationale of this study is to verify the evaluation of PK and physical characteristics of migalastat that suggests recovery in dialysate is feasible following hemodialysis, and to provide PK and safety data to allow expansion of the current Galafold® label to include end-stage renal disease (ESRD) Fabry patients with amenable *GLA* variants. Depending on characterization of PK and recovery in dialysate following hemodialysis, dose adjustment may be necessary for Fabry patients with ESRD.

#### Prediction of dialyzability for migalastat

The primary factors determining the ability of a drug to be removed by dialysis are molecular weight, protein binding, volume of distribution and red blood cell partitioning. Water solubility and ionization state at physiological pH can play a role but to a lesser extent. Migalastat is a relatively small molecule with a molecular weight of only 163.17 g/mol, well below the molecular weight (>1000 g/mol) considered to limit dialysis of small molecules. Migalastat was found to have very low to negligible binding to human plasma proteins. High plasma protein binding is associated with limiting dialyzability. High volume of distribution (>2 L/kg or ~140 L for a 70 kg subject) has been associated with poor ESRD dialyzability. In the clinical study AT1001-018, steady-state volume of distribution ( $V_{ss}$ ) for migalastat following intravenous (IV) administration ranged from 17.9 to 30.2 L (0.2 to 0.6 L/kg). Migalastat does not exhibit extensive partitioning into red blood cells, a property associated with poor dialyzability. In summary, migalastat does not exhibit any of the drug properties generally associated with poor dialyzability and, therefore, is predicted to be dialyzable.

## 7.4 Risk/benefit analysis

### Risks resulting from the IMP

Adverse reactions observed in clinical studies are provided in [Section 7.2](#).

Phase 2 clinical studies established that a dose of 150 mg administered every-other-day (QOD) provides a  $C_{max}$  of approximately 10  $\mu$ M (1631 ng/mL), the mean concentration necessary for binding and trafficking of most mutant forms of  $\alpha$ -Gal A from the endoplasmic reticulum to the lysosome. The 150 mg QOD dose was administered in Phase 3 clinical studies and is the approved dose regimen in the US, EU, and Japan for treating Fabry patients with amenable mutations.

Migalastat, a highly water soluble drug, is eliminated primarily by the kidneys. Approximately 75% of the radiolabeled dose was recovered in urine in a mass-balance study. As such, the current label restricts migalastat administration to patients with eGFR no lower than 30 mL/min/1.73m^2. After a single dose of 150 mg migalastat HCl, compared to the normal renal function group, the plasma migalastat AUC0-∞ increased 1.2-, 1.8-, and 4.3-fold in mild, moderate, and severe renal

|  |  |                                                                                             |
|--|--|---------------------------------------------------------------------------------------------|
|  |  | CRS Study No.: 090/18-03.MT
Sponsor Study No.: AT1001-035
EudraCT No.: 2018-003684-57 |
|--|--|---------------------------------------------------------------------------------------------|

function groups, respectively. The adverse event (AE) profile was similar across categories of renal impairment. The severe renal impairment group had a similar  $C_{max}$  to normal renal function, but significantly increased terminal half-life and decreased plasma clearance (Study AT1001-015). Dose adjustments in severe renal impairment based on modeling and simulations for subjects with  $eGFR < 30$  to  $\geq 15$  mL/min/1.73 m^2 suggest that the 150 mg dose administered over 4 days in subjects with  $eGFR$  from  $< 30$  to  $\geq 20$  mL/min/1.73 m^2, and over 7 days for subjects with  $eGFR < 20$  to  $\geq 15$  mL/min/1.73 m^2, would provide sufficient time to clear migalastat plasma levels to trough concentrations similar to normal renal function. For dialysis subjects, the 150 mg dose will be tested in this clinical study to determine if proper concentrations are provided for intracellular trafficking followed by removal of the majority of the dose by dialysis.

In case of overdose, general medical care is recommended. Headache and dizziness were the most common treatment-related AEs reported at doses of migalastat HCl of up to 1250 mg and 2000 mg, respectively.

There are limited data from the use of migalastat in pregnant women. Therefore, women of childbearing potential enrolled in this study have to use appropriate, reliable contraception for the study duration and for at least 30 days following (last) dosing.

A female subject is considered to be of reproductive potential (i.e., ovulating, premenopausal, not surgically sterile) if she has functional ovaries, ducts, and uterus with no impairment that would cause sterility.

This includes women with oligomenorrhea (even severe), and women who are premenopausal or who have just begun to menstruate. A female is considered to be of non-reproductive potential if she is at least 26 weeks post documented surgical sterilization (includes hysterectomy, oophorectomy, bilateral tubal ligation, or salpingectomy) or is postmenopausal and  $\geq 2$  years without menses. Female subjects who are post-menopausal  $< 2$  years must be confirmed menopausal at Screening by Follicle Stimulating Hormone (FSH) and estradiol levels, based on the central laboratory's normal ranges for women in menopause.

Transient and fully reversible infertility in male rats was associated with migalastat treatment at all doses assessed. Male subjects should maintain reliable contraceptive methods while taking migalastat.

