#### Order of recruitment

Recruitment will start with the ESRD subjects. For safety reasons, one ESRD subject will be treated first and the safety data will be discussed between sponsor and investigator. If the safety data for this individual subject is considered acceptable, the other subjects of the group will be treated in parallel.

Subjects with ESRD and matched subjects with normal renal function will be recruited in parallel but not dosed at the same time. A matched subject with normal renal function will be enrolled after the follow-up visit of his/her matched ESRD subject.

For each ESRD subject on hemodialysis, the study consists of:

- An ambulant screening period before the first treatment period (Day -21 to Day -2), during which eligibility of the subjects will be assessed.
- Two periods (each from Day -1 to Day 4) with single oral doses on Day 1 of each period. In each period, in the morning of Day-1, subjects will come to the study center for an ambulatory visit. Subjects will be hospitalized from the evening of Day -1 (~8 post meridiem [pm]) until discharge in the morning of Day 3 (after all examinations and assessments are performed). During the hospitalization period, subjects will leave the study center for dialysis. On Day 4 subjects will return to the study center for an ambulatory visit.
- An ambulant follow-up visit 7 days after last dosing for Period 2.

For each subject with normal renal function, the study consists of:

- An ambulant screening period (Day -21 to Day -2), during which eligibility of the subjects will be assessed.
- One period from Day -1 to Day 3 with a single oral dose on Day 1. In the morning of Day -1, subjects will come to the study center for an ambulatory visit. Subjects will be hospitalized from the evening of Day -1 (~8 pm) until discharge in the morning of Day 3 (after all examinations and assessments are performed).
- An ambulant follow-up visit 7 days after dosing.

Activities during the study are outlined in the flow charts in [Section 2.1](#). Sampling time points of blood, urine, and dialysate for PK are provided in [Section 2.2](#).

The duration of clinical study participation is estimated to be:

|  |  |                                                                                             |
|--|--|---------------------------------------------------------------------------------------------|
|  |  | CRS Study No.: 090/18-03.MT
Sponsor Study No.: AT1001-035
EudraCT No.: 2018-003684-57 |

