|--|--|---------------------------------------------------------------------------------------------|

- approximately 4 weeks for subjects with normal renal function (up to 3 weeks screening period followed by 8 days for treatment phase and follow-up)
- approximately 6 weeks for subjects on hemodialysis (up to 3 weeks screening period followed by at least 16 days for treatment phase and follow-up)

The study starts with first subject signing informed consent (FSI) and ends with the last subject undergoing last visit (LSO).

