#### 9.3.1 Inclusion criteria

##### 9.3.1.1 Subjects with normal renal function

Subjects must fulfill all of the following criteria to be eligible for participation in the treatment period.

|    |                                                                                                                                                                                       | Screening | Day -1 |
|----|---------------------------------------------------------------------------------------------------------------------------------------------------------------------------------------|-----------|--------|
| 1. | Healthy subjects aged 18 to 79 years                                                                                                                                                  | X         |        |
| 2. | eGFR according to MDRD equation of $\geq 80 \text{ mL/min/1.73 m}^2$ at the screening visit                                                                                           | X         |        |
| 3. | Subject is willing and able to provide written informed consent and authorization for use and disclosure of Personal Health Information (PHI) or research related health information. | X         |        |
| 4. | If of reproductive potential, both male and female subjects agree to use a medically accepted method                                                                                  | X         | X      |

 Included via Amendment 2

|  |  |                                                                                             |
|--|--|---------------------------------------------------------------------------------------------|
|  |  | CRS Study No.: 090/18-03.MT
Sponsor Study No.: AT1001-035
EudraCT No.: 2018-003684-57 |
|--|--|---------------------------------------------------------------------------------------------|

|     |                                                                                                                                                                                                                                                                                                                                                                                                                              | Screening | Day -1 |

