|-----|------------------------------------------------------------------------------------------------------------------------------------------------------------------------------------------------------------------------------------------------------------------------------------------------------------------------------------------------------------------------------------------------------------------------------|-----------|--------|
|     | of contraception during the study and for up to 30 days after dosing with migalastat.

Highly-effective methods of birth control are defined as those which result in a low failure rate, i.e. less than 1% per year, when used consistently and correctly (e.g., combination of intrauterine device and condom, sexual abstinence).

For definition of childbearing potential see Section 7.4 . |           |        |
| 5.  | Body mass index (BMI) within 18.0 to 35.0 kg/m  .                                                                                                                                                                                                                                                                                                                                                                | X         | X      |
| 6.  | In general good physical health as determined by medical and surgical history, physical examination, 12 lead ECG, vital signs, and clinical laboratory tests.                                                                                                                                                                                                                                                                | X         | X      |
| 7.  | Having had no febrile or infectious illness for at least 7 days prior to administration of the IMP of the study.                                                                                                                                                                                                                                                                                                             |           | X      |

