| 16. | If of reproductive potential, both male and female subjects agree to use a medically accepted method of contraception during the study and for up to 30 days after the (last) dose of migalastat.

Highly-effective methods of birth control are defined as those which result in a low failure rate, i.e. less than 1% per year, when used consistently and correctly (e.g., combination of intrauterine device and condom, sexual abstinence).

For definition of childbearing potential see Section 7.4 . | X         | X       |
| 17. | BMI within 18.0 to 35.0 kg/m  .                                                                                                                                                                                                                                                                                                                                                                                                                                                                                              | X         | X       |
| 18. | Having had no febrile or infectious illness for at least 7 days prior to (first) administration of the IMP of the study.                                                                                                                                                                                                                                                                                                                                                                                                                 |           | X       |
| 19. | SBP ≥90, ≤179 mmHg; DBP ≥55, ≤100 mmHg) measured after 5 min rest in supine position                                                                                                                                                                                                                                                                                                                                                                                                                                                     | X         | X       |

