Examples of such medical events include allergic bronchospasm requiring intensive treatment in an emergency room or at home, blood dyscrasias, or convulsions that do not result in in-patient hospitalization, or development of drug dependency or drug abuse.

If the following 4 elements are known, the event must be reported as described in [Section 19.4.2](#).

- Identifiable subject
- Event term
- Study drug
- Identifiable reporter

Additionally, the investigator's assessment of an event's relationship to study drug (see [Section 19.2](#)) is essential for Amicus to appropriately process the report and must be included.

|  |  |                    |                |
|--|--|--------------------|----------------|
|  |  | CRS Study No.:     | 090/18-03.MT   |
|  |  | Sponsor Study No.: | AT1001-035     |
|  |  | EudraCT No.:       | 2018-003684-57 |

Subjects must be informed and understand that they should report events meeting the definition of serious to study personnel as soon as possible (and to not wait until their next study visit).

If a non-serious event becomes serious, the change in status must be appropriately entered in the eCRF and the subject's source record, and reported to Amicus as described in [Section 19.1.2](#).

If the investigator becomes aware of an SAE that occurs more than 30 days after the last dose of study drug and considers the event possibly, probably, or definitely related to study drug, the investigator should contact the Amicus Medical Monitor to determine how the SAE should be documented and reported (see [Section 19.4.2](#)).

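### Inclusion criteria 4 and 16 word the post-dose contraception period as up to 30 days, while Section 7.4 sets at least 30 days for women of childbearing potential: a minor inconsistency

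*Protocol*

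**What the plan says.** Three places in the current protocol text set a contraception period.

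- **Section 7.4, risks resulting from the IMP.** Women of childbearing potential must use appropriate, reliable contraception for the study duration and "for at least 30 days following (last) dosing". The reason given is that data on migalastat in pregnancy are limited. Men are asked to use reliable contraception while taking migalastat; no post-dose period is given for them.
- **Section 9.3.1.1, inclusion criterion 4 (normal renal function).** One sentence covers men and women of reproductive potential, and the period it sets is worded as "of contraception during the study and for up to 30 days after dosing with migalastat".
- **Section 9.3.1.2, inclusion criterion 16 (ESRD).** The same sentence, with the period worded as "of contraception during the study and for up to 30 days after the (last) dose of migalastat".

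Both criteria are marked for checking at screening and at Day -1. Both refer to Section 7.4, but only for the definition of childbearing potential, not for the duration.

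**The concern.** *At least 30 days* is a floor. *Up to 30 days*, taken at its word, is a ceiling. A subject-protection rule is thus stated more weakly in the eligibility criteria than in the risk section that justifies it.

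The criteria are operative text. Section 9.3 allows no deviations from them and calls adherence essential, so a site that follows the eligibility table to the letter would record the weaker agreement. After the follow-up visit, 7 days after the (last) dose, the schedules of events contain no further visit or pregnancy test. For the rest of the 30 days, protection rests on what the subject has agreed to do. These subjects have no expected benefit from the drug, so the agreement should be no weaker than the minimum the protocol sets.

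**Working it through.** The protocol gives no figure to reproduce. The check is a comparison of the texts, followed by simple day counts.

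**1. Do the two durations agree?** Count days from the (last) dose.

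| Source | Who | Permitted end of contraception |
|---|---|---|
| Section 7.4 | Women of childbearing potential | Day 30 or later |
| Criteria 4 and 16, literal reading | Both sexes, if of reproductive potential | Any day from the end of the study to day 30 |
| Criteria 4 and 16, read as through day 30 | Same | Day 30 |

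The literal reading and Section 7.4 meet only at exactly day 30. The cross-reference does not settle the matter, because it covers the definition of childbearing potential only.

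**2. How large could the shortfall be?** Shortfall = 30 minus the earliest day on which stopping meets the criterion. That day depends on what *during the study* means for one subject.

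- (a) *Up to* read as through day 30: 30 − 30 = **0 days**.
- (b) *Up to* literal, *during the study* meaning the subject's own participation. The last visit is 7 days after the (last) dose; for ESRD subjects Section 9.1 lists "An ambulant follow-up visit 7 days after last dosing for Period 2". So 30 − 7 = **23 days at most**.
- (c) *Up to* literal, *during the study* meaning the whole trial, which Section 9.1 ends at the last subject's last visit. For an ESRD woman with a control, Section 9.1 says "A matched subject with normal renal function will be enrolled after the follow-up visit of his/her matched ESRD subject". The control's Day -1 therefore falls on day 7 at the earliest, the control's dose on day 8 and the control's follow-up on day 8 + 7 = 15. So 30 − 15 = **15 days at most** for her. Only the last subject in the trial could reach 30 − 7 = 23 days.

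These figures assume that the subject attends the scheduled follow-up visit.

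**3. How many subjects could be affected?** Each group of 6 has at least 2 subjects of each sex, so 2 to 4 women, and the groups are matched on sex. That gives 4 to 8 women among the 12 planned. The age range is 18 to 79 years and the protocol does not say how many will be of childbearing potential, so the number affected lies between 0 and 8.

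**4. Would exchanging the two words in the shared sentence be enough?** Each criterion is one sentence for both sexes. Replacing *up to* with *at least* there would also give men a 30-day minimum after the dose, while Section 7.4 asks of men only contraception while taking the drug. The repair has to separate the sexes or accept the stricter rule for men.

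**The case against.** The strongest reply is that nothing is missing. Section 7.4 is mandatory for every enrolled woman of childbearing potential, so one who stops before day 30 breaches the protocol whatever the criterion says. A ceiling on contraception serves no protective purpose, and *up to 30 days* is most naturally taken as through day 30. The single sentence may also have been written loosely because it covers men, for whom Section 7.4 sets no post-dose period. All of this stands and keeps the point small. It does not make the two texts agree.

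Exposure late in the window is also likely to be low. Day 7 is 168 h after the dose. At the half-life of about 4 h in Section 7.2, that is 168 / 4 = 42 half-lives. At the 32.3 h that Section 9.2 gives for severe renal impairment, it is 168 / 32.3 = 5.2 half-lives, leaving about 3% (0.5^5.2) before any removal by dialysis. The ESRD half-life is not given and may be longer, although criterion 14 requires dialysis for at least 4 h every 72 h. This supports a small practical consequence. It does not replace the 30-day minimum that the protocol chose.

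A reader might infer that the protocol lacks a 30-day safeguard, or that women are told they may stop early. The documents support neither. Section 7.4 contains the safeguard, and the consent text, which informs subjects, is not available for review. Nor does safety reporting clearly end at day 7: Section 19.1.2 reserves a special procedure for "an SAE that occurs more than 30 days after the last dose of study drug", which suggests that earlier SAEs follow the ordinary route.

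**Conclusion.** The inconsistency holds as a minor one, optional to minor in weight. Criteria 4 and 16, read literally, permit women to stop contraception before the minimum in Section 7.4. The shortfall is 0 days if *up to* means through day 30. It is at most about 23 days if it is a ceiling and the subject stops at the day 7 visit. Which reading was meant cannot be told from the protocol, and the number of women concerned may be zero. PK endpoints, sample size and analysis are untouched.

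**What to change.** In criteria 4 and 16, split the sentence by sex. Female subjects of reproductive potential agree to contraception during the study and for at least 30 days after the (last) dose. The male duration stays as it is, in a separate clause.

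Alternatively, apply at least 30 days to both sexes and acknowledge that this is stricter for men than Section 7.4.

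The cost is a wording change in two criteria, plus a check that the consent form states the same minimum for women. No data collection, visit or analysis changes.
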